### Data Collection Procedure

#### Cross-Sectional Survey: Phase 1 of the Study

One hundred (*n* = 100) patients, who meet the eligibility criteria, in the research settings will be recruited for possible participation in the study. Data collection in phase 1 will be done at each of the research settings for an estimated period of 4 weeks/rehabilitation setting. Each patient who meets the eligible criteria for phase 1 in a particular setting and who will give informed consent after a thorough explanation of what the study will entail will be included into the study and undergo the battery of audiological and physiotherapy assessment procedures (Table 1). The patients will also be informed that participation in the trial is voluntary and they are free from undue coercion. In this study, the International Classification of Functioning, Disability and Health (ICF) (25) is used as the model of disablement within which the patients’ levels of impairment, functional activity, and participation will be determined and documented. Collection of comprehensive demographic information relating to age, gender, race, affected side post-stroke, dominant side prior to stroke, stroke type, type of residence, level of education, and type of work will be collected from patients. Thereafter, an audiologist will assess (a) visual acuity (static and dynamic), (b) nystagmus, (c) saccadic eye movements, (d) smooth pursuit eye movements, (e) vestibulo-ocular reflex, and (f) saccular, utricular, and vestibular nerve function. A physiotherapist who is not involved in the treatment of these patients will assess (1) cognitive function, (2) residual oculomotor visual performance, (3) visual–perceptual system, (4) functional balance, (5) gait, (6) functional ability, and (7) presence of anxiety and/or depression in these patients. If a specific eye condition or eye disease is suspected, the patient will be referred to an ophthalmologist for ophthalmologic assessment and management. The battery of valid and standardized outcome measures that will be completed by a qualified audiologist and physiotherapist (who will not be involved in the allocation of the patients to the experimental and control groups nor the intervention) is summarized in Table 1. The qualified audiologist and physiotherapist will complete the battery of outcome measures over a 2-day period to minimize possible performance fluctuations due to fatigue as result of the lengthy test protocol.

**Table 1 T1:** **The battery of valid and standardized outcome measures that will be completed by a qualified audiologist and physiotherapist**.

Outcome measure used by the physiotherapist	Objective (phase 1)	Objective (phase 2)	Validity and reliability of outcome measure
Video nystagmography (VNG)	To determine the prevalence of visual impairments and central vestibular dysfunction in patients who sustained a stroke measured by the assessment of (a) nystagmus, (b) saccadic eye movements, and (c) smooth pursuit eye movements	To determine the effect of the combination of VRT and VSE integrated with task-specific activities received by patients in Group 1 compared with patients in Group 2 who received task-specific activities alone on their (a) visual impairments, (b) central vestibular dysfunction, (c) nystagmus, (d) saccadic eye movements, and (e) smooth pursuit eye movements after the intervention period of 2 weeks	Video nystagmography (VNG) records eye movements using digital video image technology to quantify (a) nystagmus, (b) saccadic eye movements, and (c) smooth pursuit eye movements (26)
EyeSeeCam vHIT	To determine the prevalence of visual impairments and central vestibular dysfunction in patients who sustained a stroke measured by the assessment of the vestibulo-ocular reflex	To determine the effect of the combination of VRT and VSE integrated with task-specific activities received by patients in Group 1 compared with patients in Group 2 who received task-specific activities alone on their (a) visual impairments, (b) central vestibular dysfunction, and (c) vestibulo-ocular reflex after the intervention period of 2 weeks	Measurements of the HIT with the EyeSeeCam vHIT quantify the VOR-deficit and detect the presence of corrective saccades (2, 27). The head impulse test presents with sensitivity (84%) and specificity (82%) (2, 27)
Vestibular-evoked myogenic potential (VEMP), cervical vestibular-evoked myogenic potential (cVEMP), and ocular vestibular-evoked myogenic potential (oVEMP)	To determine the prevalence of visual impairments and central vestibular dysfunction in patients who sustained a stroke measured by the assessment of the saccular (cVEMP), utricular (oVEMP), and vestibular nerve function	To determine the effect of the combination of VRT and VSE integrated with task-specific activities received by patients in Group 1 compared with patients in Group 2 who received task-specific activities alone on their (a) visual impairments, (b) central vestibular dysfunction, and (c) saccular, utricular, and vestibular nerve function after the intervention period of 2 weeks	Intraclass correlation coefficient (ICC) values ranged between 0.78 and 0.96 and CV_ME_ values ranged from 4 to 36% for P1 and N1 latency, threshold, and interpeak amplitude (28). ICC values of 0.65–0.68 and CV_ME_ values of 170–189% were obtained for the asymmetry ratio (28)
LogMar chart – static visual acuity	To determine the prevalence of visual impairments and central vestibular dysfunction in patients who sustained a stroke measured by the assessment of visual acuity (static)	To determine the effect of the combination of VRT and VSE integrated with task-specific activities received by patients in Group 1 compared with patients in Group 2 who received task-specific activities alone on their (a) visual impairments, (b) central vestibular dysfunction, and (c) visual acuity after the intervention period of 2 weeks	The LogMar chart that follows the principle of logarithmic size progression during the assessment of visual acuity is “considered to be the gold standard for the assessment of distant vision” (29). No differences were noted between test and retest measurements of aided visual acuity (*t* = −0.048, *p* = 0.96) or unaided visual acuity (*t* = −0.038, *p* = 0.97); therefore, the LogMar chart has no learning effect. Test–retest measures of aided and unaided visual acuity are highly correlated, *r* = 0.72 (*p* = 0.000) and *r* = 0.84 (*p* = 0.000) (30)
LogMar chart – dynamic visual acuity	To determine the prevalence of visual impairments and central vestibular dysfunction in patients who sustained a stroke measured by the assessment of the vestibulo-ocular reflex	To determine the effect of the combination of VRT and VSE integrated with task-specific activities received by patients in Group 1 compared with patients in Group 2 who received task-specific activities alone on their (a) visual impairments, (b) central vestibular dysfunction, and (c) vestibulo-ocular reflex after the intervention period of 2 weeks	Provides an objective, behavioral assessment of vestibulo-ocular reflex (VOR) function in response to rotational head movement stimuli. The Dynamic Visual Acuity test (DVA) assesses visual acuity during head movement relative to baseline static visual acuity assessed by the LogMar chart. Unilateral vestibular hypofunction (UVH) (*n* = 41), 10 with UVH mean age = 49.4 (15.5); range 19–70 years: the frequency of head motion affects clinical DVA scores in patients with UVH. DVA scores significantly decreased as head motion frequency increased from 0.5 to 1.0 Hz and from 1.0 to 1.5 Hz, during horizontal (yaw) and vertical (pitch) head movements with both vision charts (*p* < 0.001). Research evidence suggests that DVA be administered with horizontal and vertical rotational head movements of at least 1.5 Hz with the LogMar chart (31)
Mini-Mental State Examination	To determine the association between the presence of visual impairments and central vestibular dysfunction on the patients’ cognitive function. Patients must score at least 7/30 on this scale to be included into the study	To determine the effect of the combination of VRT and VSE integrated with task-specific activities received by patients in Group 1 compared with patients in Group 2 who received task-specific activities alone on their (a) visual impairments, (b) central vestibular dysfunction, and (c) cognitive function after the intervention period of 2 weeks	The MMSE has significant correlates with the Barthel Index (32) assessing activities of daily living, the Montgomery Asberg Depression Rating Scale (MADRS) (33), and the Zung Depression Scale (34, 35). The internal consistency of the MMSE ranged from (alpha = 0.54–0.96) (36). McDowell et al. (37) reported the internal consistency of the MMSE was adequate (alpha = 0.78) (37). Twenty-four studies reported test–retest reliability (*r* > 0.75) for the MMSE (36)
Vula eye health mobile application	To determine the prevalence of visual impairments and central vestibular dysfunction in patients who sustained a stroke measured by the assessment of visual acuity and screening of the patients’ eye health condition	To determine the effect of the combination of VRT and VSE integrated with task-specific activities received by patients in Group 1 compared with patients in Group 2 who received task-specific activities alone on their (a) visual impairments, (b) central vestibular dysfunction, (c) visual acuity, and (d) eye health condition after the intervention period of 2 weeks	The researcher did not find any publication with regard to the mobile application’s validity and reliability in the stroke population but decided to include this measure because visual acuity and eye health condition are very important visual function to determine because intervention in phase 2 of the study need to take a patient’s visual acuity and eye health condition into consideration when implementing the patient’s intervention
			If a specific eye condition or eye disease is suspected, the patient will be referred to an ophthalmologist for ophthalmologic assessment and management
King-Devick Test © (4)	To determine the association between the presence of visual impairments and central vestibular dysfunction on the patients’ residual oculomotor visual performance	To determine the effect of the combination of VRT and VSE integrated with task-specific activities received by patients in Group 1 compared with patients in Group 2 who received task-specific activities alone on their (a) visual impairments, (b) central vestibular dysfunction, and (c) residual oculomotor visual performance after the intervention period of 2 weeks	The King–Devick (K–D) test is a <2-min bedside test that requires saccadic eye movements for rapid visual performance measurement. Although the test is quick to perform, the researcher did not find any publication with regard to the test’s reliability in the stroke population. Moster et al. (38) reported that total time values were significantly higher compared with the control group (*p* = 0.003). Increased K–D scores were associated with decreased values for binocular low-contrast (*p* < 0.001) and high-contrast visual acuity (*p* = 0.003). It is therefore recommended that the K–D test be included in the battery of valid and standardized outcome measures completed by a qualified physiotherapist during phase 1 and phase 2 of the study
Star cancelation test (4)	To determine the association between the presence of visual impairments and central vestibular dysfunction on the patients’ visual–perceptual function	To determine the effect of the combination of VRT and VSE integrated with task-specific activities received by patients in Group 1 compared with patients in Group 2 who received task-specific activities alone on their (a) visual impairments, (b) central vestibular dysfunction, and (c) visual–perceptual function after the intervention period of 2 weeks	Plummer et al. noted that Marsh and Kersel reported the correlation between the Line Bisection Test with the Star Cancellation Test (Pearson *r* = −0.40, *p* = 0.02) in (*n* = 27) stroke patients (39). The star cancellation test correlated with other clinical tests of unilateral spatial neglect, indicating a construct validity of (Pearson *r* = 0.26–0.78) (39). Bailey et al. reported the sensitivity of the star cancelation test = 76.4% compared with other copying tests (57.5%) (40)
Berg balance scale	To determine the association between the presence of visual impairments and central vestibular dysfunction on the patients’ functional balance (static)	To determine the effect of the combination of VRT and VSE integrated with task-specific activities received by patients in Group 1 compared with patients in Group 2 who received task-specific activities alone on their (a) visual impairments, (b) central vestibular dysfunction, and (c) functional balance after the intervention period of 2 weeks	The Berg Balance Scale (BBS) has an excellent test–retest reliability (ICC = 0.88) (41). The BBS correlated with other functional measurements in various older adults with disability; Barthel Index (Pearson *r* = 0.67, *n* = 31), Fugl-Meyer Test motor and balance subscales (Pearson *r* = 0.62–0.94, *n* = 60), Timed Up, and Go Test (TUG) scores (Pearson *r* = 0.76, *n* = 31) and the Dynamic Gait Index (Spearman coefficient = 0.67, *n* = 44) (42)
Dynamic gait index (DGI) (7, 34)	To determine the association between the presence of visual impairments and central vestibular dysfunction on the patients’ gait (dynamic balance)	To determine the effect of the combination of VRT and VSE integrated with task-specific activities received by patients in Group 1 compared with patients in Group 2 who received task-specific activities alone on their (a) visual impairments, (b) central vestibular dysfunction, and (c) gait after the intervention period of 2 weeks	McConvey and Bennett (43) reported inter-rater reliability (ICC for total DGI = 0.983), with individual test items ranging from 0.910 to 0.976 in patients with MS (*n* = 10). Intrarater reliability ranged from 0.760 to 0.986 and an inverse correlation (−0.801) between gait speed on a 6.1 m course and total DGI score (43). Lin et al. (44) reported good test–retest reliability (ICC > 0.94; 0.91–0.97) in stroke patients (*n* = 48) (44). Jonsdottir and Cattaneo (45) reported good test–retest reliability (ICC = 0.96) and individual items varied from 0.56 (gait and pivot turns) to 1.00 (stair climbing) in chronic stroke patients (*n* = 25) (45)
Barthel index (BI) (4)	To determine the association between the presence of visual impairments and central vestibular dysfunction on the patients’ functional ability	To determine the effect of the combination of VRT and VSE integrated with task-specific activities received by patients in Group 1 compared with patients in Group 2 who received task-specific activities alone on their (a) visual impairments, (b) central vestibular dysfunction, and (c) functional ability after the intervention period of 2 weeks	The Barthel Index’s (BI) calculated inter-rater reliability using the intraclass correlation (ICC) = 0.94 and the internal consistency using Cronbach’s alpha ranges between 0.89 and 0.92. The BI also closely correlated with the Berg Balance Scale and the Fugl-Meyer motor assessment in patients with stroke (Pearson’s correlation coefficient *r* ≥ 0.78) (46)
			Hsueh et al. reported inter-rater reliability for individual items (kappa value range, 0.53–0.94) and total score (ICC = 0.94) of the BI in stroke patients (*n* = 121). The BI correlated with the Fugl-Meyer Motor Assessment (Pearson’s *r* ≥ 0.78, *p* < 0.0001) the Frenchay Activities Index (Pearson’s *r* ≥ 0.59, *p* < 0.0001) (46)
Hospital anxiety and depression scale	To determine the association between the presence of visual impairments and central vestibular dysfunction on the patients’ level of anxiety and depression	To determine the effect of the combination of VRT and VSE integrated with task-specific activities received by patients in Group 1 compared with patients in Group 2 who received task-specific activities alone on their (a) visual impairments, (b) central vestibular dysfunction, and (c) level of anxiety after the intervention period of 2 weeks	Correlation between the HADS and the BDI ranges from *r* = 0.61 to 0.83. Correlation between the General Health Questionnaire, the Clinical Anxiety Scale, and the HADS ranged from *r* = 0.50 to 0.68 and *r* = 0.69 to 0.75, respectively. The HADS presents with an internal consistency with a Cronbach’s alpha of 0.85 (47)
Telephonic-administered international physical activity questionnaire (IPAQ)	To determine the association between the presence of visual impairments and central vestibular dysfunction on the patients’ participation in physical activity	To determine the effect of the combination of VRT and VSE integrated with task-specific activities received by patients in Group 1 compared with patients in Group 2 who received task-specific activities alone on their (a) visual and ocular impairments and (b) central vestibular dysfunction post-stroke’s participation in physical activity 20 weeks after rehabilitation has been terminated	Correlation between the telephonic-administered IPAQ compared with a face-to-face administered IPAQ was found to be 0.92 for the section on leisure-time, and 0.87 for the section on transport-related activities (48). The telephone interview reliability kappa was 0.78 (48)
			Reliability data for the IPAQ short questionnaires (*n* = 1974): repeatability is at an acceptable level, with 75% of the correlation coefficients observed above 0.65 and ranging from 0.32 to 0.88 (49)

#### Cross-Sectional Clinical Trial: Phase 2 of the Study

Patients with or without visual impairment and/or vestibular dysfunction will be identified based on the results of patients’ diagnosis after the battery of standardized outcome measures has been completed by two independent assessors (audiologist and physiotherapist) during phase 1 of the study. Sixty patients with (visual and/or vestibular dysfunction) identified in phase 1 of the study will be recruited to participate in the second phase of the study and randomly allocated to either Group 1 or Group 2. The study population will include the data of the first 30 patients in each group who participate in the study for all 20 weeks. The two groups of 30 patients in the respective group do not make provision for drop out of participants in the study. If patients leave the study for any reason, they will have to be replaced by another patient. The results of this first battery of tests (phase 1) will serve as the baseline measurements for phase 2 of the study. In phase 2, the researcher will determine the effect of the combination of VRT and VSE integrated with task-specific activities (*n* = 30) as an intervention approach for patients in the sub-acute phase post-stroke compared with patients who will receive task-specific activities (*n* = 30) alone as an intervention approach on their: (a) visual impairments, (b) central vestibular dysfunction, (c) cognitive function, (d) residual oculomotor visual performance, (e) visual–perceptual system, (f) functional balance, (g) ability to modify gait in response to changing task demands, (h) functional ability, and (i) presence of anxiety and/or depression after the intervention period of 2 weeks. The consecutive assessment will be repeated by the two independent assessors after the 2-week intervention period. Twenty weeks after rehabilitation has been terminated, the physiotherapist (independent assessor) will contact all patients who completed phase 2 of the study, to complete the Telephonic-Administered International Physical Activity Questionnaire (IPAQ). The aim will be to determine the effect of the combination of VRT and VSE integrated with task-specific activities for patients in Group 1 (experimental group), compared with patients who will receive task-specific activities alone Group 2 (control group) on patients’ participation activities 20 weeks after rehabilitation has been terminated.

Patients will receive intervention daily for a period of 2 weeks. The period of intervention consisting of 2 weeks was selected due to the fact that patients are on average admitted to a private rehabilitation setting post-stroke for a period of 2 weeks. The intervention period of 2 weeks were further decided upon because results from a previous study (12) demonstrated a statistically significant (*p* = 0.02) difference between Group 1 and Group 2 after 2 weeks intervention (12). Any adverse effects within the period of 20 weeks will be documented.

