### Data Management and Analysis

Data of the cross-sectional survey (phase 1 of the study) will be analyzed and reported according to the STROBE checklist. Data of the cross-sectional clinical trial (phase 2 of the study) will be analyzed and reported according to the CONSORT statement. The outcomes measures measuring the clinical outcomes the data summary will make use of descriptive statistics, geometric mean, SD, median, range, and 95% CIs will be used when data conforms to a Gaussian distribution. Results from the two groups will be compared with respect to outcome at 2 weeks, adjusted for baseline values, using analysis of covariance (ANCOVA), using ranks when data are skewed. Data characteristics permitting, groups may also be compared using a mixed-model approach which will indicate the data over all the time points where treatment, time, and treatment–time interaction will be entered into the model, and the treatment–time interaction will be of primary intent. Testing will be done at the 0.05 level of significance.

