#### Limitations of the Study

•Upon completion of the previous study by the authors, a large number of drop out of participants after discharge from various rehabilitation settings in South Africa was observed limited long-term follow-up despite the fact that participants received remuneration for traveling costs and were contacted telephonically on a regular basis. The large loss to follow-up prevented the researcher from determining whether the long-term effect of the treatment was sustained and was regarded as a limitation of the previous study.•Twenty weeks after rehabilitation has been terminated, the physiotherapist (independent assessor) will contact all patients who completed phase 2 of the study, to complete the Telephonic-Administered International Physical Activity Questionnaire (IPAQ) to determine the effect of the combination of VRT and VSE integrated with task-specific activities for patients in Group 1 (experimental group), compared with patients in Group 2 (control group) who will receive task-specific activities alone on their participation activities 20 weeks after rehabilitation has been terminated.

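### The phase 2 study population keeps only the first 30 patients per group who stay for all 20 weeks and replaces those who leave, which leaves the 2-week Barthel comparison open to retention bias

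*Protocol article*

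**What the plan says.** The section on the phase 2 clinical trial takes 60 people found in phase 1 to have a visual or vestibular deficit and divides them at random between the two arms. It then defines who is analysed: "The study population will include the data of the first 30 patients in each group who participate in the study for all 20 weeks". By the article's own account, the planned numbers "do not make provision for drop out of participants in the study". A substitution rule takes the place of such an allowance: "If patients leave the study for any reason, they will have to be replaced by another patient".

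The main comparison comes much earlier than 20 weeks. Data Management and Analysis says: "Results from the two groups will be compared with respect to outcome at 2 weeks", with baseline adjustment by ANCOVA. The Sample Size section powers the trial on the Barthel change from baseline at 2 weeks. The Abstract makes training of rehabilitation teams depend on the Barthel result. According to Table 1 and the phase 2 section, the only later measurement is the telephone IPAQ, 20 weeks after rehabilitation has ended.

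Under Limitations, the article reports that in the authors' previous study "a large number of drop out of participants after discharge from various rehabilitation settings in South Africa was observed". It gives no figure.

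**The concern.** Read as written, the rule makes a patient's 2-week Barthel result count only if that patient is still in the study months after the result was recorded. Nothing in the 2-week question requires this. Retention is an event after randomisation, and both recovery and the treatment received can affect it. The groups compared would be those who stayed, topped up with others, and not the groups formed by random allocation.

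Unequal retention is plausible here. The principal investigator treats every experimental patient, while centre physiotherapists treat the controls (Interventions). The authors also expect loss after discharge to be a problem. At stake is the result that decides whether the intervention is taught to rehabilitation staff.

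**Working it through.** **Inputs from the Sample Size section.** Planned effect 0.214 on the log10 scale (change at 2 weeks); SD of change 0.249; power 90%; significance level 0.05; 30 per group. The phase 2 section gives a dropout allowance of zero.

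**Step 1. Reproduce the plan's figure.**
n per group = 2 × (1.960 + 1.282)² × 0.249² / 0.214² = 28.5, so 29 by the normal approximation. The noncentral t calculation gives 30, with power of 90.5%. The stated 30 per group therefore reproduces as a two-sided test with no loss. The size is not the fault; the analysis set is.

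**Step 2. Who is removed.** To obtain 30 completers, an arm with loss d needs on average 30/(1−d) patients. This is 33.3 (34) at 10% loss and 42.9 (43) at 30%. Under the rule, the excess (4 and 13 patients) leaves the analysis, including any whose 2-week outcome had been observed.

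**Step 3. Size of the possible bias.** The documents give no loss rate, so loss and its correlation ρ with 2-week change are assumptions. Suppose patients with worse change are more likely to leave. Among those who stay, mean change rises by ρ × SD × φ(z)/(1−d), where z is the normal quantile of d.

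- φ(z)/(1−d) is 0.195 at d = 10%, 0.350 at 20% and 0.497 at 30%.
- Loss of 30% versus 10%: 0.497 − 0.195 = 0.302 SD. Multiplied by 0.249, this is 0.075 × ρ/1, giving 0.023 at ρ = 0.3 and 0.038 at ρ = 0.5.
- Loss of 20% versus 10%: 0.350 − 0.195 = 0.155 SD, giving 0.012 and 0.019.
- Equal loss, or ρ = 0: the difference is zero.

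**Step 4. Effect on the test.** The simulation used 20,000 runs, 30 completers per arm, SD 0.249, no true effect and a t-test on change.

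| Loss by arm | ρ | Spurious difference (log10) | Share of 0.214 | Two-sided error |
|---|---|---|---|---|
| 20% vs 20% | 0.3 to 0.5 | none | 0% | 5.0% |
| 20% vs 10% | 0.3 to 0.5 | 0.012 to 0.019 | 6–9% | 5.4–6.1% |
| 30% vs 10% | 0.3 to 0.5 | 0.023 to 0.038 | 11–18% | 6.2–9.4% |
| 30% vs 10% | 0 | none | 0% | 5.1% |

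The spurious difference favours the arm with more loss. One-sided error in that direction is 9.6–15.4% at 30% versus 10%. The closed form in step 3 and the simulation agree.

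**The case against.** The strongest reply is that the rule creates a risk of bias and not a bias. That stands: equal loss, or loss unrelated to outcome, does no harm to the comparison. Baseline-adjusted ANCOVA would also remove selection that acts through baseline severity. The simulation did not model this, so its figures apply to selection that remains after adjustment. The previous study's loss is unquantified and may not carry over, since the 20-week contact here is a single telephone questionnaire.

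Several stronger readings are tempting, but the documents do not support them.

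- A reader might infer that replacements enter the vacated arm without randomisation, and that their allocation can be predicted. The article says only that another patient takes the place. Continued randomisation until both groups fill also fits the wording. If replacements do go into the vacated arm, they are not randomised, so the text needs to settle this.
- A reader might infer that fast recoverers are removed because "patients are on average admitted to a private rehabilitation setting post-stroke for a period of 2 weeks". That is an average for private settings, and public institutions take part too. Nothing requires the repeat battery before discharge. A patient without a 2-week assessment has missing data under any analysis set.
- A reader might infer a contradiction with the commitment to CONSORT. That is a commitment about reporting and does not fix an analysis set.
- Larger bias figures can be produced, such as 0.350 × 0.179 = 0.063 or 0.497 × 0.179 = 0.089. These need loss in one arm only, driven wholly by outcome. They also set the single-time SD of 0.179 against an effect on change that the Sample Size section pairs with 0.249.
- A reader might infer that phase 1 cannot supply enough patients, since 70% of 100 is 70 and 1 − 60/70 allows only 14% loss. The article says at least 100 patients and a prevalence above 70%, so 70 is near a floor. Supply is also a separate matter of feasibility.

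What the reply does not remove is the rule itself. It is explicit, it fixes the analysis population, and no other section provides for analysing all randomised patients.

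**Conclusion.** The concern holds. The article makes the 2-week Barthel comparison depend on remaining in the study to 20 weeks, and it would discard observed 2-week outcomes for no gain. Confidence is high that the rule is stated and is unsound for this comparison. The size and direction of any bias cannot be fixed from the documents.

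The 11–18% of the planned effect and two-sided error of about 6–9% rest on three assumptions: loss of 30% versus 10%, a correlation of 0.3 to 0.5 with 2-week change, and no true effect. At 20% versus 10% the inflation is small. It should be corrected before the data are analysed, and preferably before any patient is replaced, because later analysis cannot make a substitute placed in a known arm a randomised patient.

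**What to change.** 1. Remove the 20-week condition and the replacement rule from the definition of the phase 2 population for the 2-week analysis.
2. Analyse every randomised patient in the allocated group for the 2-week outcomes, whatever the 20-week status.
3. If more patients are wanted, allocate further eligible phase 1 patients only through the same random sequence, to either arm. Say so in the text.
4. Confine 20-week completeness to the IPAQ analysis, with a missing-data sensitivity analysis and reasons for loss reported by arm.

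The cost is a change of wording and one sensitivity analysis. The arms may not be exactly 30 and 30, and fewer than 60 patients may have 20-week data. For the 2-week comparison, only loss before the 2-week assessment then reduces power. With 27, 24 or 21 assessed per arm in place of 30, two-sided power by the normal approximation falls from 91% to about 88%, 84% or 79%. If the sponsor wishes to protect against that, N/(1−d) gives 30/0.9 = 34 per arm at an assumed 10% loss and 30/0.8 = 38 at 20%.
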